### Plans to promote participant retention and complete follow-up {18b}

During the consent-taking process, participants are informed about the maximum time commitment needed for the study. This ensures that participants can commit to all the sessions in the study regardless of their group assignment and to reduce participant withdrawals after the groups are assigned. Furthermore, immediately upon group assignment, participants will be scheduled for all subsequent sessions. This minimises the chances of session cancellations since participants can do advance planning of their own schedule. Experimenters will send reminder emails and messages before each session to ensure that participants are aware of and well-prepared for the upcoming session. Moreover, they will also actively engage with the participants throughout the study and provide flexible alternatives for rescheduling whenever possible.

### Data management {19}

Researchers from the NTU-CLIC team will be responsible for data entry and analyses. Participants will be assigned a subject identification number so that data collected at different stages of the study can be linked to the corresponding participant. Records of potential participants that had contacted the recruitment team to express their interest in joining the study will be kept in an Excel sheet to ensure that progress and status of recruitment are being tracked closely. This Excel sheet includes the number of potential participants that contacted the recruitment team, inclusion/exclusion criteria status, withdrawal, and completion of the study participation.

Data collected as part of the research participation will be downloaded from the respective platforms used. Non-computerised tasks will be manually recorded and keyed into Excel spreadsheets. Quality checks will be performed routinely by the research team to ensure that data is proper. The data are then kept on a secured server that only the research team and other approved personnel can access. The researchers are responsible for the data maintenance and analyses.

### Confidentiality {27}

The data collected has been kept securely in a server that is accessible only by the IRB-approved research team and approved personnel. A list of personnel who are allowed access is submitted to the NTU-IRB. Additionally, the data collected are in accordance with Singapore’s Personal Data Protection Act. Participants will be assigned an identification number that are with no relation to identifiable personal data. A list of ID matching to each participant’s personal data are kept separate and are only accessible by a few personnel in the research team.

### Plans for collection, laboratory evaluation and storage of biological specimens for genetic or molecular analysis in this trial/future use {33}

N/a. Biological specimens are not collected in this study.

## Statistical methods

### Statistical methods for primary and secondary outcomes {20a}

#### Quantification of Structure Learning training outcomes

Most Structure Learning training outcomes are computed as in Wang et al.. [34, 43] As the Structure Learning training programme assesses contingency learning, trial task accuracy will not be useful to assess learning. Instead, learning is assessed in a probabilistic manner. We will compute a PI for each context within each training block (see Fig. 2 for more information on the context-to-target contingencies) to quantify the minimum overlap between the participant response distribution and the presented stimuli target distribution. The overall PI for a specific training block is then derived by taking the contingency-weighted average PI across all possible contexts. We will also adjust this PI measure for random guess baseline to derive a normalised PI measure.

Besides assessing learning, we will also quantify the main strategies employed by the participants during Structure Learning training sessions. The Kullback–Leibler (KL) divergence index will be used to compare participant response distribution to a probability matching and probability maximising distribution separately. Participants who engaged in greater matching will have a response distribution that closely matches the presented target distribution across all context-target pairings, i.e. if context A is followed by target B 80% of the time and target C 20% of the time, participant will pick target B in 80% of the trials and target C 20% of the trials for a perfect matching response distribution. Participants who engaged in greater maximising will have a response distribution where the most likely outcome is always chosen, i.e. if context A is followed by target B 80% of the time and target C 20% of the time, participants will always choose target B for a perfect maximising response distribution. The model difference quantified by KL divergence index is referred to as strategy choice wherein negative values indicate a strategy closer to matching and positive values indicate a strategy closer to maximising. A strategy choice is derived per training block and strategy fluctuations can be tracked across training blocks and sessions for each participant. We will then attempt to derive a general index that can reflect participant’s selection of strategy for each training session. For each individual participant, we will compute this strategy index, herein termed strategy integral curve difference (strategy ICD) by taking the difference between the integral of each participant’s strategy curve with the integral of the exact matching curve.

#### Evaluation of efficacy of Structure Learning training

We will primarily evaluate the efficacy of Structure Learning training by examining differences in post-test measures for EF between Control and Training groups. Measures will be either standardised for easier interpretations or normalised whenever possible. Means and standard deviations of either a suitable population reported in published studies or the large-scale study that is concurrently carried out by CLIC to characterise the latent construct of CF, herein termed as WP0.1, will be used for data normalisation. Parametric tests will be used to compare group differences of primary outcome measures whenever possible. Besides focusing on individual primary outcomes, we will also examine group differences with a combination of primary outcome measures that best characterise the latent constructs of cognitive flexibility, working memory, and inhibition in the structural equation modelling outcomes of WP0.1. A multivariate mixed effects model will be used to account for the nested data structure and to investigate differences between Training and Control group on these combined EF measures.

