
#### Secondary behavioural outcomes

Secondary behavioural outcomes in the context of the present study are mainly outcomes that we are planning to investigate potential cross-domain far-transfer benefits of the Structure Learning training. These different tasks and key variables of interest are listed in Table 2.

**Table 2 Tab2:** Secondary behavioural tasks and variables of study

Construct/domain	Task	Variables/subtasks
Demographics, Social & Psychological variables	Social questionnaires	• Perceived Stress Scale
		• Pittsburgh Sleep Quality Index
		• Empathy Quotient
		• Social Value Orientation
		• Prisoner’s Dilemma
		• Trust Game
		• Risk Preference
		• Ambiguity Aversion
		• Personal Relative Deprivation Scale
		• Cooperativeness and Competitiveness Personality Scale
		• Tolerance of Uncertainty
		• Multilingualism
		• Perceived Social Support
		• Big Five Inventory
		• Creative Mindset
Language & Numeracy	Woodcock Johnson IV (WJIV)	• Letter-Word Identification
		• Applied Problems
		• Passage Comprehension
		• Calculation
		• Sentence Reading Fluency
		• Maths Facts Fluency
General Intelligence	Raven’s Advanced Progressive Matrices (RAPM)	• Total correct
		• Change in accuracy score
	Wechsler Abbreviated Scale of Intelligence (WASI) Vocabulary	• Total score
	Wechsler Abbreviated Scale of Intelligence (WASI) Block Design	• Total score
Creativity	Verbal Fluency	• Mean fluency score
		• Clustering coefficient
		• Average shortest path length
		• Modularity
	Alternate Uses Task	• Total fluency score
		• Total originality score
		• Total flexibility score
	Remote Associates Test	• Percentage of correct solutions

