## Assignment of interventions: allocation

### Sequence generation {16a}

The allocation sequence is controlled with an algorithm written in R and we employ variance minimisation procedures [55] to match age, sex, intelligence and cognitive flexibility while randomly allocating participants to either the Training or Control group. Intelligence is assessed using the RAPM score, while cognitive flexibility is assessed through the switch cost in accuracy and reaction time on the CST. Both intelligence and cognitive flexibility measures are collected during the Baseline Cognitive Session. The matching algorithm script is executed only when participants within a recruitment batch have all completed the Baseline Cognitive Session. Data from the previous batches of recruited participants is considered during the group allocation. This approach ensures that the two groups remain matched on pre-specified matching variables with each batch of incoming new participants.

Participant data for each matching measure are first collated into a source Excel file. Group assignment for the first recruitment batch is done sequentially upon initialisation of the algorithm. Once the number of assigned participants reaches the number of groups present, i.e. two in the present study, subsequent participants are temporarily assigned to one group at a time. For each potential group assignment, we compute the mean of each matching measure within each group and thereafter derive a mean of means between groups as well as the sum of squared deviations of this group mean. The end goal of the algorithm is to achieve the best minimal sum of squared deviations of this group mean by exploring all possible group allocation of a particular participant. We ensure a balance group allocation of 1:1 (Training vs. Control) by constraining the algorithm such that it will not assign a new participant to the same group as the previous participant.

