#### Examining performances in Structure Learning training and its relation to cognitive flexibility

We will examine how performances in Structure Learning training affect post-test cognitive flexibility measures. As participants go through multiple training sessions, they will need to learn varying underlying contingencies and adjust their strategies in order to solve the task. A mixed effects model will be used to model the changes in PI and strategy ICD across training sessions so that we can examine how these changes affect post-test CF measures. Measures collected during the Baseline Cognitive Session 1 and Pre-test Cognitive Session 2 will be entered as covariates in the model.

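### The post-test group comparison names no covariates, although groups are formed on age, sex, RAPM and CST switch costs; adjusting for these would gain precision at almost no cost

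*Protocol article*

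**What the plan says.** **Allocation** (Sequence generation {16a}): "we employ variance minimisation procedures [55] to match age, sex, intelligence and cognitive flexibility". The measures used are specific: "Intelligence is assessed using the RAPM score, while cognitive flexibility is assessed through the switch cost in accuracy and reaction time on the CST". With age and sex that makes five variables, all recorded before anyone is allocated. The same section adds a balancing rule for the algorithm: "it will not assign a new participant to the same group as the previous participant".

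**Design** (Trial design {8}): most primary and secondary measures are taken only at post-test, to avoid practice effects. The section gives this as the reason why matching matters for the post-test comparison.

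**Efficacy analysis** (Evaluation of efficacy of Structure Learning training): group differences on post-test measures are the main evidence. For single outcomes, "Parametric tests will be used to compare group differences of primary outcome measures whenever possible". For combined outcomes, "A multivariate mixed effects model will be used to account for the nested data structure". No covariate is named for either.

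**Covariates elsewhere** (Examining performances in Structure Learning training and its relation to cognitive flexibility): "Measures collected during the Baseline Cognitive Session 1 and Pre-test Cognitive Session 2 will be entered as covariates in the model". This sentence belongs to the model that relates learning during training to later cognitive flexibility, not to the group comparison.

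**Repeated measures** (Outcomes {12}; Table 2): CST and RAPM are measured at both times. For RAPM, Table 2 lists "Change in accuracy score" beside the total correct.

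**The concern.** The group comparison depends on a design feature that its analysis does not carry through. The five variables were chosen because they are expected to relate to executive function. With outcomes measured once, after training, they are an obvious source of extra precision, and they cost nothing further to collect.

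Two things are at stake. The first is power, in a trial of about 100 evaluable participants. The second is the calibration of the test: when allocation forces balance on prognostic variables, a test that ignores them uses too large a standard error.

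There is also a smaller point of discipline. Who will be blinded {17a} says that analysts know the group assignments. If the adjustment set is left open, it can be chosen after group results have been seen.

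**Working it through.** **Inputs.** From Sample size {14}: 50 evaluable per group, alpha 0.05, d = 0.25, correlation 0.3 between pre-test and post-test. Sidedness is not stated; two-sided is assumed. R² of the five allocation variables is not given; the values tried are assumptions, except 0.09 = 0.3². The value d = 0.5 is also an assumption.

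**1. The plan's own figure.** The stated 46 per group is for a Group × Time interaction. The usual noncentrality is λ = f²·N·2/(1 − ρ). With f = 0.25 and N = 46 in total, λ = 0.0625 × 46 × 2/0.7 = 8.21 and power is 80.0%, so the formula gives 46 in total (23 per group). Reading 0.25 as d (f = 0.125) gives 178 in total, or 89 per group. The figure therefore does not reproduce as worded, and it does not describe a post-test comparison. That is a separate matter; only the 50 per group, d and the correlation are used below.

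**2. Power of the post-test comparison.** Noncentrality is δ = d/√[(1 − R²)·2/n]. With n = 50, √(2/50) = 0.2, so unadjusted δ = 2.5 at d = 0.5 and 1.25 at d = 0.25, on 98 degrees of freedom. Five covariates leave 93, which moves the critical value only from 1.984 to 1.986.

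| R² | Sample-size equivalent 1/(1 − R²) | Power, d = 0.5 | Power, d = 0.25 |
|---|---|---|---|
| unadjusted | 1.00 | 69.7% | 23.6% |
| 0.09 | 1.10 | 73.7% | 25.4% |
| 0.20 | 1.25 | 79.0% | 28.2% |
| 0.35 | 1.54 | 86.6% | 33.5% |

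**3. Size of the plain test.** With perfect balance, the true size of a nominal 5% unadjusted test is about 2[1 − Φ(1.96/√(1 − R²))]: 3.9% at R² = 0.1 and 1.9% at R² = 0.3. A simulation (50 per group, five independent, equally weighted covariates, 2,500 runs per setting, Monte Carlo error about 0.4 points) gave:

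- sequential minimisation: 4.2% at R² = 0.1 and 2.7% at R² = 0.3
- minimisation within pairs: 2.1% at R² = 0.3
- ANCOVA: 4.6-5.4%
- plain t-test under strict alternation: 5.3-5.5%

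The last line matters because the rule in {16a} against giving consecutive participants the same group, read literally, forces alternation and leaves minimisation nothing to choose.

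**4. RAPM change score.** At correlation r, the variance relative to post-test only is 2(1 − r) for change and 1 − r² for ANCOVA. At r = 0.3 these are 1.40 and 0.91, a ratio of 1.54. At d = 0.5 and 50 per group, power is about 55% for change, 70% for post-test only and 74% for ANCOVA. The ratio simplifies to 2/(1 + r), which exceeds 1 for every r below 1, so the preference for ANCOVA does not depend on r being 0.3.

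**The case against.** The strongest reply is that the protocol never calls the test unadjusted. Its sentence sets parametric against non-parametric methods; ANCOVA is parametric; and an article may leave a covariate list to the full analysis plan. This stands in part. That the comparison is unadjusted is an inference from the contrast with the next section, which does name covariates. What remains is that the stated plan permits a plain t-test in a trial whose comparability rests on these variables, and that a better choice is available from data in hand.

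Four stronger readings are tempting, and the document does not support them:

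- A reader might infer that CST is to be analysed by Group × Time or by change. Group × Time appears only in the sample-size basis, the efficacy section compares post-test scores, and a change score is listed only for RAPM, a secondary outcome.
- A reader might infer that the plain test's standard error is wrong. That holds only if allocation truly balances the factors, and the error is then conservative. Type I error is not inflated. Chance imbalance is not a validity defect either, because an ordinary test already allows for it.
- A reader might expect a gain worth 25-54% more participants. That needs R² of 0.20-0.35. The protocol's only relevant correlation implies about 10%, and the pre-test RAPM's reported Cronbach's alpha of 0.59 limits what RAPM can explain.
- A reader might take these variables to be the main precision available. WASI and WJIV scores are also collected before training, and no R² is given for any measure.

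**Conclusion.** The point holds as an improvement to the analysis, not as a threat to validity. The efficacy section names no covariates, the allocation variables are collected before allocation, and adjusting for them gains precision under either reading of the allocation rule. The gain is modest at the protocol's own correlation (about 4 points of power at d = 0.5, about 2 at d = 0.25) and substantial only if R² reaches 0.20 or more. It does not rescue the stated effect size: at d = 0.25, power stays near one third even at R² = 0.35.

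The correction of a conservative standard error is conditional on minimisation working. The figures rest on a two-sided 5% test, 50 evaluable per group, and assumed values of R² and of d = 0.5.

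**What to change.** In the efficacy section, define the group comparison for each primary outcome as an ANCOVA of the post-test score on group, adjusted for age, sex, baseline RAPM, and baseline CST switch cost in accuracy and in reaction time. Enter the same five covariates in the multivariate mixed model.

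Analyse post-test CST and RAPM in the same way; their own baselines are already in the set. For RAPM, use this in preference to the change score in Table 2. Keep the unadjusted test as a sensitivity analysis.

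In {16a}, reconcile the rule on consecutive assignments with the minimisation, so that it is clear which allocation was used.

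The cost is a change of wording and five degrees of freedom with about 100 participants. No new data are needed.

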#### Examining performances in Structure Learning training and its relation to cognitive flexibility

We will examine how performances in Structure Learning training affect post-test cognitive flexibility measures. As participants go through multiple training sessions, they will need to learn varying underlying contingencies and adjust their strategies in order to solve the task. A mixed effects model will be used to model the changes in PI and strategy ICD across training sessions so that we can examine how these changes affect post-test CF measures. Measures collected during the Baseline Cognitive Session 1 and Pre-test Cognitive Session 2 will be entered as covariates in the model.

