**Discussion:**

We reported the development of a novel training programme based on Structure Learning that aims to hone a general learning ability to potentially achieve extensive transfer benefits across various cognitive constructs. Potential transfer benefits can be exhibited through better performance in outcome measures between Training and Control participants, and positive associations between training performance and outcomes after the training in Training participants. Moreover, we attempt to substantiate behavioural findings with evidence of neural changes across different imaging modalities by the Structure Learning training.

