### Eligibility criteria {10}

Inclusion criteria for the study are healthy volunteers of all sexes, aged between 18 and 55 years (inclusive), who have provided written informed consent to participate in the study. Exclusion criteria are as follows: (1) current and/or prior history of learning disabilities, neurological disorder, psychiatric disorder, and/or cardiovascular disorder; (2) predominantly left-handed; (3) contraindications for MRI safety (e.g. presence of pacemakers, implanted pumps, and/or metal objects in the body); (4) claustrophobia; (5) pregnancy; (6) lactation; and/or (7) pronounced visual or auditory impairments.

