### Outcomes {12}

In the present study, multiple behavioural tasks are administered to measure various cognitive constructs. Primary behavioural constructs under investigation include Structure Learning, cognitive flexibility, inhibition, and working memory. Secondary behavioural constructs under investigation include creativity, intelligence, problem-solving, language skills, numeracy skills, social tendencies, and decision making. These measures are conducted only at pre-test assessment, i.e. baseline, only at post-test assessment, i.e. after the end of structure learning training and approximately 2 months from pre-test assessment, or at both pre-test and post-test assessments. Specifically, we administered secondary behavioural constructs measuring language skills, numeracy skills, and intelligence (with the exception of the Raven’s Advanced Progressive Matrices) only at pre-test assessments as they are traits that remain relatively stable across the adult lifespan. We administered primary and secondary behavioural constructs measuring cognitive flexibility (with the exception of the Colour Shape Task), inhibition, working memory, creativity, and problem-solving only at post-test assessments to eliminate possibility of practice effects. Finally, matching tasks, i.e. Colour Shape Task and Raven’s Advanced Progressive Matrices, secondary behavioural constructs that measure social tendencies and decision making (and hence more impervious to practice effects) and all secondary neuroimaging constructs are measured at both pre and post-test assessments. Both the Control and Training groups undergo the same measures at pre and post-test assessments. However, measures for Structure Learning are collected only for the Training group. In addition, we investigate potential neural benefits of the Structure Learning training by assessing secondary neuroimaging outcomes both structurally and functionally. Detailed information regarding the individual tasks used this study can be found in Appendix B in the supplementary information.

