### Recruitment {15}

A multi-pronged approach is used for recruitment. This includes placement of physical posters across different university campuses and disseminating recruitment advertisements on social media platforms such as Telegram and Facebook. Participants are screened twice to ensure that they meet the inclusion and exclusion criteria of the study. In the first screening round, participants are requested to complete a brief online questionnaire. This questionnaire collects basic screening criteria such as age, sex, nationality, information on pre-existing health condition, and critical MRI contraindications. Experimenters will carefully review responses from the first screening round and invite eligible participants to proceed to the second round of screening,

In the second round of screening, participants are invited to complete a more detailed online screening questionnaire. This questionnaire includes more in-depth health screening questions and the Edinburgh Handedness Inventory [54] to gather additional information on participants’ eligibility. After reviewing responses, eligible participants are recruited in batches and promptly contacted to schedule the first Baseline Cognitive Session. This batch recruitment approach ensures effective management and allocation of available manpower and facilitates the matching of participants into Training and Control groups. Participants who do not meet the eligibility criteria will be informed.

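### The model linking training performance to post-test cognitive flexibility draws its covariates from the two cognitive sessions and so, on a plain reading, omits age and sex; part of a positive association could reflect age

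*Protocol article*

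**What the plan says.** Under Statistical methods {20a}, the section on performance in Structure Learning training and its relation to cognitive flexibility sets out the model: "A mixed effects model will be used to model the changes in PI and strategy ICD across training sessions", so as to examine how those changes bear on post-test flexibility. Its covariate rule is one sentence: "Measures collected during the Baseline Cognitive Session 1 and Pre-test Cognitive Session 2 will be entered as covariates in the model".

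Trial design {8} and Participant timeline {13} describe the cognitive sessions before training as covering intelligence, baseline cognitive flexibility, language and numeracy. Age and sex come from elsewhere. Recruitment {15} says of the first-round online screening form: "This questionnaire collects basic screening criteria such as age, sex, nationality". Sequence generation {16a} uses minimisation "to match age, sex, intelligence and cognitive flexibility while randomly allocating participants", and of these four variables it places only intelligence and cognitive flexibility in the Baseline Cognitive Session.

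Outcomes {12} adds that "measures for Structure Learning are collected only for the Training group". The Discussion paragraph of the abstract lists, among the ways in which transfer may show itself, "positive associations between training performance and outcomes after the training in Training participants".

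**The concern.** This model uses no randomised contrast. It compares Training participants who learned more with Training participants who learned less. Minimisation balances age and sex between the arms. It leaves the spread of age inside the Training arm as it was, and eligibility allows 18 to 55 years.

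If younger participants both learn the sequences better and switch tasks better, training performance and post-test flexibility will correlate even when the training transfers nothing. The protocol's own background refers to age-related cognitive decline. All flexibility tasks except the Colour Shape Task are given only at post-test, so stable age differences in those tasks cannot be removed by taking change scores. Control therefore rests on the covariates, and two of the four variables that the trial chose to match on are not among those named. At stake is a positive slope read as support for transfer when part of it is age.

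**Working it through.** The protocol gives no figure for this association and no age correlations, so there is nothing to reproduce. What follows is a range under assumptions.

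**Inputs from the protocol.** Sample size {14}: 60 per group with 20% attrition, so 60 × 0.80 = 48 in the Training arm; alpha 0.05 (two-sided assumed). Covariates inferred from Outcomes {12}, Table 2 and Sequence generation {16a}: RAPM 1 + Colour Shape Task switch costs 2 + WASI subtests 2 + WJIV subtests 6 = 11. The list of tasks by session is in Appendix B, which is not shown, so 11 is an inferred count.

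**Assumed.** Age correlates with training performance and with post-test flexibility at the same size r, and there is no true link between the two.

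**Spurious slope, baseline scores unrelated to age.** With standardised variables and age as the only connection, the slope is r × r:
- r = 0.2: 0.04
- r = 0.3: 0.09
- r = 0.4: 0.16
- r = 0.5: 0.25

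**Spurious slope, baseline scores that track age.** Let k baseline scores each correlate b with age and be related to one another and to the outcome only through age. The share of age variance left unexplained is v = 1 / (1 + k·b²/(1 − b²)), and the slope is r²·v / (1 − r²·(1 − v)). For r = 0.5 and k = 3:
- b = 0.3: v = 1/(1 + 3 × 0.09/0.91) = 0.77; slope = 0.25 × 0.77/(1 − 0.25 × 0.23) = 0.20
- b = 0.5: v = 1/(1 + 3 × 0.25/0.75) = 0.50; slope = 0.125/0.875 = 0.14
- b = 0.7: v = 1/(1 + 3 × 0.49/0.51) = 0.26; slope = 0.25 × 0.26/(1 − 0.25 × 0.74) = 0.08

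Simulated mean slopes agree at n = 50 (0.206, 0.144, 0.079) and n = 60 (0.204, 0.141, 0.077).

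**False-positive rate, simulated.** Linear regression of post-test flexibility on one training score and 11 cognitive covariates, n = 48:

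| Age correlation r | Scores absorb almost none | Scores absorb much | Age and sex added |
|---|---|---|---|
| 0.2 | 5–6% | about 5% | about 5% |
| 0.3 | 8% | about 5% | about 5% |
| 0.4 | 14–16% | 6–7% | about 5% |
| 0.5 | 29–33% | 7–10% | about 5% |

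In the second column, at most RAPM is weakly related to age and no covariate predicts the outcome. In the third, baseline switch cost correlates 0.6 with post-test flexibility and relates to age as strongly as post-test flexibility does, and four other scores correlate −0.3 to −0.5 with age.

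Intermediate assumptions give intermediate rates. At r = 0.5 the rate is 16% if baseline switch cost and four other scores all track age at −0.3. It is 19% if five scores track age at −0.3 and none predicts the outcome. What protects the model is baseline flexibility that carries the age effect. If it predicts the outcome but is unrelated to age, the rate at r = 0.5 with weakly age-related other scores stays near 30%.

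**The case against.** The strongest reply is that the covariate sentence does not say that nothing else may enter. A journal article often leaves the final list to an analysis plan, and neither that plan nor Appendix B is shown. A reader might infer that the protocol excludes age and sex; it does not say so. What stands against the reply is that the protocol does state where the covariates come from, that source does not supply age or sex, and no other section adds them to this model.

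A reader might also infer that a false-positive rate near 30% is to be expected. The documents do not support that. The covariates already include baseline flexibility and intelligence, which should take up part of any age effect. Recruitment through universities, polytechnics and social media may give a sample younger and narrower in age than the eligibility limits, with weaker age correlations. The simulation also uses one training score per person, whereas the plan models changes in PI and strategy ICD across sessions, and nothing in the documents links age to those changes. These points stand, and they lower the likely size.

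Sex has no stated mechanism as a confounder here. Its case is consistency with the matching variables only.

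Finally, the abstract joins this association to a between-group difference and does not say that either suffices alone, and efficacy is judged primarily between groups. That limits the consequences. It does not make the within-arm estimate free of age.

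**Conclusion.** The point holds in a limited form. As written, the covariate rule omits age and sex from a non-randomised, within-arm model, and between-arm matching does not make up for this. Age could account for some of a positive association.

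The size is uncertain and may be small. Under assumed age correlations of 0.2 to 0.5 with both variables, the false-positive rate goes from about 5% to 7–10% if baseline scores absorb much of the age effect. A rate near 30% needs correlations of 0.5 together with baseline scores that absorb little or almost none of it. All of these correlations are assumptions.

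It would be wrong to infer that the main efficacy result is compromised. The Training versus Control comparison of post-test measures does not use this model and is unaffected.

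**What to change.** In the section on training performance and cognitive flexibility, add age and sex to the covariates, so that the model contains all four matching variables as well as the Session 1 and 2 measures. Age is the main concern; sex is added for consistency. If this is already intended, the sentence should say so. Describe the result as an adjusted association within the Training group, not by itself as evidence of transfer.

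The cost is one sentence and two degrees of freedom; the data are already collected. In a simple regression with 48 participants, an intercept, one training score and 11 covariates leave 48 − 13 = 35 residual degrees of freedom, and adding age and sex leaves 33. If that is tight, combining the six WJIV subtests into a language and a numeracy composite frees 6 − 2 = 4, which is better than dropping a matching variable.
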